## Abstract

**Introduction:**

Cardiovascular diseases represent the leading cause of mortality worldwide. This category includes cerebrovascular disease, ischemic heart disease, and peripheral vascular disease. Secondary prevention is effective for patients with a history of cardiovascular events, with antihypertensives, statins, and acetylsalicylic acid being the most prescribed drugs. Therapeutic adherence is crucial, as the lack of it increases morbidity, mortality, reduces quality of life, and raises healthcare costs. However, less than half of patients adhere to all three drugs within the first year post-event. Furthermore, non-adherence is more pronounced in primary care.

**Objective:**

Based on our hypothesis that in patients undergoing cardiovascular secondary prevention, an intervention grounded in the application of the Chronic Care Model improves adherence to the three preventive drugs, this study aims to evaluate the efficacy of a health education intervention, which implements this model, to increase adherence in patients with cardiovascular disease.

**Methods:**

An open-label randomized controlled trial will be conducted, selecting patients who meet inclusion criteria through consecutive non-probability sampling. Random assignment will be performed using the random number table method. Based on a therapeutic adherence rate of 50% in the control group and 80% in the intervention group, with a type I error of 5% (95% confidence interval), a type II error of 20% (80% power), and accounting for a 15% loss to follow-up, the final sample size will be of 45 patients per group. Follow-up will last for 1 year. Following data collection, univariate, bivariate, and multivariate analyses will be performed to isolate confounding factors and assess the intervention’s impact on adherence.

**Discussion:**

If the results obtained in this study are favorable and the intervention is successful in enhancing therapeutic adherence, its applicability would be substantial, representing a feasible intervention for implementation in primary care. This approach addresses a significant public health issue, namely the lack of therapeutic adherence and its associated consequences. Moreover, this is particularly pertinent for high-risk patients, such as those in secondary prevention, given that cardiovascular disease remains the leading cause of mortality in developed countries. This trial has been registered at clinicalTrials.gov, https://clinicaltrials.gov/study/NCT06510946.

## Introduction

1

Therapeutic adherence (TA) refers to the extent to which patients comply with therapeutic recommendations. The physician-patient relationship, once grounded in a paternalistic model, has evolved over the past few decades into a model of shared responsibility. Consequently, when discussing TA, co-responsibility serves as a fundamental pillar, acting as a cornerstone for decision-making and self-management of the disease. For this shift to occur, the relationship between patients and healthcare professionals must be based on trust and dialog.

Moreover, TA not only refers to the extent to which patients appropriately use drugs, but its dimension is also generally related to health. For this reason, it is necessary to distinguish between compliance, persistence, and TA (1), as these terms are not synonymous. Currently, it is preferable to specify the term lack of TA rather than noncompliance, since the latter implies that only patients are responsible for the treatment and the degree to which they appropriately follow the prescribed dosage. However, TA requires active patients who are knowledgeable about their disease, understand the prescribed treatments, and recognize the importance of adherence. Finally, therapeutic persistence relates to the time during which the patient continues the treatment, that is, the time that elapses from the initiation to the interruption of treatment (2).

The World Health Organization (WHO) defines adherence to long-term treatments by merging the concepts from Haynes and Rand as follows: “as the extent to which a person’s behavior–taking medication, following a diet, and/or executing lifestyle changes–corresponds to recommendations agreed with a healthcare provider” (3).

Cardiovascular disease (CVD) is the leading cause of early mortality across most European populations, including Spain (4), and is also the most common cause of mortality worldwide (5). Within the spectrum of CVD, cerebrovascular disease, ischemic heart disease, and peripheral vascular disease are included.

Secondary prevention is an effective strategy for patients who have experienced previous events, with the most commonly used drugs being antihypertensives, lipid-lowering agents, and antiplatelet and/or anticoagulant treatments, along with lifestyle changes. Nevertheless, TA in these patients is often low, jeopardizing the effectiveness of such interventions. Although it is usually better than in primary prevention. In example, in a meta analysis, adherence was 50 and 66% for primary and secondary CV prevention studies, respectively (6).

In a study conducted in Spain involving 92,436 patients (62% men, mean age 72 years) with cardiovascular events, of whom 60.5% presented with stroke, 30.6% with myocardial infarction and 8.9% with revascularization were included. Drugs for secondary prevention were antiplatelets, angiotensin-converting enzyme (ACE) inhibitors/Angiotensin II receptor blockers (ARBs) and statins. Lack of adherence was defined as medication abandonment. Less than half of patients adhere to all three drugs within the first year post-event. Information was obteined from electronic medical records in real practice (7).

Multiple factors contribute to TA issues, often interrelated. Patient-related factors include age, sex, race, socioeconomic status, employment situation, forgetfulness, educational level, and personal beliefs regarding their illness, such as disagreement with the diagnosis and treatment costs. Healthcare professional-related factors encompass inadequate communication skills, insufficient follow-up, poor healthcare professional-patient relationships, and lack of clarity in prescribed instructions. Disease-related factors may involve acute or chronic conditions, comorbidities, mental health issues, and fatigue from prolonged treatments. Treatment-related factors include dosage, duration, type of recommendations (pharmacological or lifestyle changes), number of drugs, dosage forms, and side effects. Family and social environment characteristics also play a role, where supportive networks can enhance TA, while certain beliefs or cultural factors may hinder it. Lastly, healthcare system-related factors such as time constraints, frequent changes of healthcare providers, poor coordination among them, waiting lists, consultation conditions, and lack of digitalization can adversely affect TA (8).

No single intervention has been conclusively shown to improve TA independently. However, a combination of strategies may enhance adherence. Various approaches have been implemented, including health education, motivational interviewing, reminder phone calls, simplified dosing regimens, medication compliance aids (MCAs), packaging labels and pharmacological combinations such as polypills (9).

In chronic diseases, non-adherence to hygienic-dietary recommendations ranges from 70 to 95% (10), while adherence to pharmacological treatments is approximately 50% (11); however, although pharmacological treatments represent the foremost strategy currently available for the prevention and management of chronic diseases, adherence to these therapies remains below anticipated levels and continues to present significant challenges for both healthcare professionals and patients. TA also differs between patients with symptomatic and asymptomatic conditions. In asymptomatic patients, there is often a belief that they do not need the medication, which can contribute to poor adherence (12). This can vary based on age, pathology, or other factors, highlighting the magnitude of this problem. It is estimated that in secondary prevention, more than one-third of patients discontinue treatment after 6 months, and around half do so within a year (6). This is particularly relevant in CVD within primary care, where up to 39.4% of patients abandon prescribed treatments compared to 22.4% in hospital care (13).

Chronic illnesses pose substantial challenges for patients and their caregivers, particularly in the realm of disease management. The Chronic Care Model (CCM) (14) addresses these challenges by advocating for proactive, integrated, and patient-centered approaches to care and health education. It underscores the importance of patient engagement in self-management, encompassing participation in health-promoting activities, adherence to treatment protocols, and effective communication with healthcare providers. The CCM facilitates systematic assessments, preventive interventions, and psychosocial support, with the objective of enhancing health outcomes by addressing both clinical and emotional needs.

The objective of this study is to evaluate the efficacy of an intervention through health education based on the CCM implementation to increase TA in patients with secondary prevention for CVD.

## Materials and methods

2

### Aims and objectives

2.1

The primary aim of this study is to evaluate the efficacy of an intervention through health education based on the Chronic Care Model’s implementation to increase TA in patients with secondary prevention for CVD.

Other secondary objectives are:Evaluate the efficacy of an intervention based on the implementation of the CCM on the control of cardiovascular risk factors (CVRF).Assess whether the intervention affects the improvement of patients’ quality of life.Determine TA in patients undergoing secondary prevention for CVD.Compare differences in TA based on sex, age, race, and education level.Identify modifiable factors associated with poor TA.

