### Participants

2.3

A total of 90 patients undergoing secondary prevention for CVD will be recruited from a health center in Alicante, Spain. The target population will consist of patients undergoing secondary prevention for CVD who are receiving treatment with statins, (ACE) inhibitors/ (ARBs) at a single daily dose, and acetylsalicylic acid (ASA). The inclusion criteria are: (1) adults of both sexes, aged 18 years or older, who provide written informed consent after reading the patient information sheet; (2) patients receiving daily single-dose (ACE) inhibitors/ (ARBs), ASA, and statins for at least 6 months as part of secondary prevention; (3) diagnosis of cerebrovascular disease, ischemic heart disease or peripheral vascular disease; (4) patients under regular follow-up at our health center; and (5) patients identified with suboptimal therapeutic adherence, defined by the Haynes-Sackett test supplemented with a Medication Possession Ratio (MPR) < 80% for any of the three drugs in the past 6 months. The exclusion criteria include: (1) refusal to participate; (2) incomplete consent form; (3) language barriers; (4) psychiatric, psychological, neurological, or social conditions that impair the ability to participate in the intervention or follow-up; (5) life expectancy of less than 1 year; (6) patients whose drug management is handled by a caregiver (professional or family member); (7) Barthel Index score < 60; (8) institutionalized patients; and (9) patients currently enrolled in similar research studies.

Patients from our health center will be contacted by telephone, selecting those patients recorded in the electronic medical records with a coded diagnosis according to the International Classification of Diseases, Tenth Revision (ICD-10) of cerebrovascular disease, ischemic heart disease, and peripheral vascular disease in secondary prevention for CVD, who are prescribed all three drugs and meet the inclusion criteria while not presenting any exclusion criteria outlined in the study protocol. They will be informed about the study, and those who confirm their participation will be scheduled for an in-person appointment (with a companion, if possible, to also involve them in the intervention).

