During the first consultation with the principal investigator, patients will be invited to participate in the study, proceeding to verify compliance with the selection criteria. To evaluate TA, the Haynes-Sackett test will be administered, supplemented by the MPR from the medical history, reviewing the year prior to the consultation. The purpose of the research will be explained, along with informed consent and its signing. Additionally, a patient information sheet will be provided.

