### Study variables

2.6

The main variable to evaluted will be TA using the Haynes-Sackett test to determine adherence vs. non-adherence (a dichotomous qualitative variable), complemented by the MPR to calculate a percentage (a continuous quantitative variable). Good TA is defined as responding that the patient experiences no difficulties taking all prescribed tablets and has an MPR > 80% for the three preventive drugs. Conversely, if these conditions are not met, it is classified as poor TA. Poor TA, based on the MPR, is indicated if the patient has not picked up 20% or more of the prescribed packages from the pharmacy in recent years. A diagnosis of poor TA can be made using either method. Since three TA are analyzed, poor TA is established if it occurs with any one of them, two, or all three.

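### Secondary objective 3 asks for adherence in secondary-prevention patients, but the trial enrols only poor adherers; objectives 4 and 5 hold only within that group

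*Protocol article*

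**What the plan says.** Section 2.1 (Aims and objectives) sets five secondary objectives. The third is "Determine TA in patients undergoing secondary prevention for CVD" and the fourth is "Compare differences in TA based on sex, age, race, and education level". The fifth is to identify modifiable factors associated with poor TA. None of the three is limited to poor adherers or given its own time point.

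Section 2.3 (Participants) begins broadly: "The target population will consist of patients undergoing secondary prevention for CVD who are receiving treatment with statins" and the other two drug classes. Inclusion criterion 5 then narrows the sample to "patients identified with suboptimal therapeutic adherence, defined by the Haynes-Sackett test supplemented with a Medication Possession Ratio (MPR) < 80% for any" preventive drug, with a 6-month look-back. Those telephoned are patients "who are prescribed all three drugs and meet the inclusion criteria while not presenting any exclusion criteria outlined in the study protocol", so no unrestricted cohort is described.

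At the first consultation, where eligibility is verified, TA is measured: "To evaluate TA, the Haynes-Sackett test will be administered, supplemented by the MPR from the medical history, reviewing the year prior to the consultation".

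Section 2.6 (Study variables) counts TA as good only if the patient reports no difficulty with the tablets and "has an MPR > 80% for the three preventive drugs". Failure on either method, or for any one drug, is poor TA. MPR is also kept as a continuous percentage. Section 2.2 places assessment of primary and secondary variables at 1 year, with an evaluation at 6 months.

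**The concern.** Objective 3 asks for the level of TA in a population, and criterion 5 removes the good adherers from that population before anyone is enrolled. An estimate from the 90 randomised patients therefore describes the entry filter at baseline, and the filter plus the intervention at 12 months. Objectives 4 and 5 inherit the restriction. Among patients who all start as poor adherers, a comparison by sex or education shows whose adherence recovered, not who adheres in secondary prevention generally.

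What is at stake is interpretation. Section 2.7 plans descriptive percentages with 95% confidence intervals throughout, and the limitations in the Discussion do not mention the restriction to non-adherers. The Discussion offers random assignment as the safeguard against selection bias by sex, age, race and education. Randomisation balances the two arms; it does not make the sample represent the patients screened out by criterion 5.

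**Working it through.** **1. Baseline.** Good TA (section 2.6) needs both a satisfactory Haynes-Sackett answer and MPR above 80% for all three drugs. Criterion 5 needs a failure on adherence, with MPR below 80% for at least one drug. A patient who meets criterion 5 fails the definition of good TA over the same window. So good TA is about 0/90 = 0%, overall and in every stratum of sex, age, race and education. A few exceptions are possible because criterion 5 looks back 6 months while the first-consultation review covers a year.

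**2. Twelve months.** Inputs: planning rates of 50% (control) and 80% (intervention) from section 2.8, read here as 12-month rates, and equal arms of 45.

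- Pooled TA = 0.5 × 50% + 0.5 × 80% = 65%.
- With 2:1 allocation in favour of the intervention it would be (2/3) × 80% + (1/3) × 50% = 70%.

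The pooled value thus depends on the allocation ratio and is not a property of secondary-prevention patients. That 65% lies next to the 66% quoted in the Introduction for secondary-prevention studies is a coincidence.

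**3. The plan's own sample size.** With p̄ = 0.65, two-sided α = 0.05 and 80% power:

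n = [1.96·√(2 × 0.65 × 0.35) + 0.8416·√(0.5 × 0.5 + 0.8 × 0.2)]² / 0.30² = (1.322 + 0.539)² / 0.09 = 38.5, so 39 per group.

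Then 39 × 1.15 = 44.9, or 45; dividing by 0.85 gives 46. The stated 45 is reproduced to within one patient. The present point does not depend on it.

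**4. Precision at 12 months.** Evaluable after 15% loss: 45 × 0.85 = 38.25, so 38 per arm and 76 in all. Control-arm TA of 19/38 = 50% has a Wilson 95% interval of about 35% to 65%. Even that arm describes only patients selected as poor adherers.

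**5. Power for objective 4.** Take 76 evaluable patients, mean TA of 65%, two subgroups, a two-sided 5% test and no adjustment. The subgroup splits are assumptions: 50:50, and 62:38 (62% is the share of men in the Spanish study cited in the Introduction).

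For an even split and a 20-point difference (75% v 55%):

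- null SE = √(2 × 0.65 × 0.35 / 38) = 0.1094
- alternative SE = √[(0.75 × 0.25 + 0.55 × 0.45) / 38] = 0.1070
- power = Φ[(0.20 − 1.96 × 0.1094) / 0.1070] = Φ(−0.135) = 0.446

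| Difference | 50:50 split | 62:38 split |
|---|---|---|
| 10 points | 15% | 14% |
| 20 points | 45% | 43% |
| 30 points | 80% | 76% |

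Education has five levels, so an even spread would leave about 76 / 5 ≈ 15 patients per level.

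**The case against.** A reader might infer that objective 4 cannot be met at all. The documents do not support that. TA can vary again by 1 year; age, sex, race, education and group are listed variables (section 2.6.1); and section 2.7 plans a multivariate analysis of TA adjusted for them. A model of 12-month TA with arm and these factors is close to what is already planned. This stands, and it limits the point on objective 4 to its population and power.

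A reader might also infer that nothing varies at baseline. Only the yes/no composite is nearly constant. Continuous MPR can differ between patients and between drugs, since criterion 5 needs a shortfall for only one of the three. This stands too.

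A third inference is that the trial will publish 0% as adherence in secondary prevention, with a bias as large as the literature figures. No such report is planned. Objective 3 has no time point, and the below-half figure in the Introduction defines non-adherence as abandonment of medication, not by Haynes-Sackett plus MPR. No size of bias against those figures is claimed here.

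Finally, a full protocol or analysis plan might name an analysis set for objective 3. But the conflict lies between two explicit statements in the article, the objective and the entry criterion. No choice of time point within the randomised sample resolves it.

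**Conclusion.** The concern holds in full for objective 3. The randomised sample cannot give the level of TA in secondary-prevention patients: baseline good TA is about 0% by design, and 12-month TA (65% pooled if the planning rates hold) belongs to initially non-adherent patients, half of them treated.

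It holds in part for objectives 4 and 5. They can be addressed at 12 months or with continuous MPR, conditional on poor adherence at entry. Power is about 45% for a 20-point difference and reaches about 80% only at 30 points with an even split. These power figures rest on 76 evaluable patients, a mean TA of 65% and the assumed splits; more uneven subgroups would do worse.

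The primary comparison, the randomisation and the sample size are not affected. The matter is still worth correcting before analysis, because following the plan as written yields an estimate that does not answer the stated objective.

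**What to change.** Delete objective 3, or restate it as: *estimate, by arm, the proportion with good TA at 12 months among secondary-prevention patients with suboptimal TA at entry*.

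Restate objectives 4 and 5 as comparisons of 12-month TA in that same population, adjusted for arm. Label them as low-powered, and make no claim about TA in secondary prevention generally. Add the restriction to initially non-adherent patients to the limitations.

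Optionally, keep a coded screening log and report MPR before criterion 5 is applied, for patients with the qualifying diagnosis and all three drugs. This should be called MPR-based possession, not TA, because protocol TA also needs the Haynes-Sackett answer. It can be broken down only by factors that the record holds; the article does not say that race and education are among them. It would use data from people who have not consented, so ethics approval must be confirmed to cover it first.

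The restatement costs a few lines of text and no patients, visits or measurements. The price is narrower secondary objectives. The optional log adds record work and possibly an ethics amendment.

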### Study design

2.2

Open label randomized controlled trial, selecting patients presenting the inclusion criteria through consecutive non-probability sampling. The participants will be randomly assigned to either the intervention or control groups using a random number table. An intervention will be conducted on a group of patients (intervention group), and its outcomes will be compared to those of the control group, which will receive standard follow-up under routine clinical practice conditions. The follow-up will last for 1 year, at the conclusion of which the primary and secondary variables will be assessed. Nevertheless, an evaluation will be conducted at 6 months, and if significant benefits are evident, the study will be terminated.

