### Statistical analysis

2.7

The data will be analyzed using version 23.0 of the Statistical Package for the Social Sciences (SPSS), developed by IBM Corp. (Armonk, NY) for Windows, and the analysis will be performed with masking of third parties.

First, a univariate descriptive analysis will be conducted for qualitative variables, expressed as percentages, and for quantitative variables, expressed as means and standard deviations, with 95% confidence intervals calculated in all cases. Additionally, a bivariate analysis will be performed to identify associations between the intervention and changes in the parameters outlined in the study objectives, with particular focus on TA. Finally, a multivariate analysis will be carried out to isolate potential confounding factors and assess the impact of the intervention on TA, adjusted for the remaining studied variables. Statistical significance will be established with a *p*-value of less than 0.05.

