### Sample size calculation

2.8

Based on a TA rate of 50% in the control group and 80% in the intervention group, with a type I error of 5% (95% confidence interval), a type II error of 20% (80% power), and accounting for a 15% loss to follow-up, the final sample size will be of 45 patients per group.

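### The binding 6-month stop for significant benefit, with 0.05 the only level stated, does not hold the 5% type I error and can displace the 1-year primary assessment

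*Protocol article*

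**What the plan says.** Section 2.2 (Study design) of the protocol article fixes the time of the main comparison: "The follow-up will last for 1 year, at the conclusion of which the primary and secondary variables will be assessed". It then qualifies this: "an evaluation will be conducted at 6 months, and if significant benefits are evident, the study will be terminated". That sentence is binding in form, but it names no variable, test or significance level for the 6-month decision.

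Section 2.7 (Statistical analysis) gives one level and ties it to no particular analysis: "Statistical significance will be established with a *p*-value of less than 0.05".

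Section 2.8 (Sample size calculation) starts from adherence rates ("Based on a TA rate of 50% in the control group and 80% in the intervention group"), sets the error rates ("with a type I error of 5% (95% confidence interval), a type II error of 20% (80% power"), allows for dropout ("accounting for a 15% loss to follow-up") and concludes that "the final sample size will be of 45 patients per group". It mentions no interim test.

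Section 2.4 (Intervention group) schedules two of the four group sessions after the 6-month evaluation, at months 9 and 12.

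**The concern.** These statements do not fit together. A trial that ends on a significant result at 6 months, and otherwise tests again at 12 months, has two opportunities to declare benefit. If each uses 0.05, the overall chance of a false-positive result exceeds the 5% on which the sample size is built.

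A second consequence does not depend on the error rate. If the rule fires, the 1-year assessment is not made and the last two group sessions are not delivered. The trial would then report a 6-month comparison of part of the intervention in place of the 1-year comparison it sets out to make. In a trial of 90 patients, an estimate taken because it crossed a threshold early also tends to be too large.

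**Working it through.** **Inputs from the article.** Adherence 50% versus 80%, type I error 5%, power 80%, loss 15%, 45 per group (2.8); significance at p<0.05 (2.7); one evaluation at 6 months with a stop for benefit, and primary assessment at 1 year (2.2).

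**Assumed, not in the article.** The 0.05 level applies at 6 months; the final test is two-sided; the 6- and 12-month test statistics have correlation r, varied from 0 to 0.95.

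**Step 1: reproduce the sample size.** For two proportions with pooled variance under the null, no continuity correction, and mean rate 0.65:

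n = [1.96·√(2·0.65·0.35) + 0.842·√(0.25 + 0.16)]² / 0.30² = (1.322 + 0.539)² / 0.09 = 38.5, so 39 evaluable per group.

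Allowing for loss, 39 × 1.15 = 44.9 gives 45, and 39/0.85 = 45.9 gives 46. The arcsine formula gives 38 evaluable, and 38/0.85 = 44.7 gives 45. The stated 45 is therefore a single-test design using the full 5%.

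**Step 2: type I error with the stop.** Let Z1 and Z2 be standard normal under the null with correlation r, and c = 1.96. The trial declares a difference if Z1 > c (stop for benefit) or, failing that, if |Z2| > c at 12 months:

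overall error = 0.025 + 0.05 − P(Z1 > c and |Z2| > c)

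false claim of benefit = 0.025 + 0.025 − P(Z1 > c and Z2 > c)

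| r | overall error | false claim of benefit |
|---|---|---|
| 0 | 7.4% | 4.9% |
| 0.5 | 0.075 − 0.0046 = 7.0% | 0.050 − 0.0046 = 4.5% |
| 0.7 | 0.075 − 0.0083 = 6.7% | 0.050 − 0.0083 = 4.2% |
| 0.9 | 0.075 − 0.0148 = 6.0% | 0.050 − 0.0148 = 3.5% |
| 0.95 | 5.7% | 3.2% |

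With one test at 12 months the two columns would read 5% and 2.5%. Simulated binary outcomes agree. With 38 per arm and outcome correlation 0.3 to 0.9, the overall error is 7.3% to 6.1%, against about 5.0% for the final test alone. With 45 per arm it is 6.6% to 5.3%, against about 4.5% for the final test alone, because the test on counts is slightly conservative at that size.

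**Step 3: chance of stopping at 6 months.** Exact binomial power of the uncorrected chi-square test at 0.05, with 38 and 45 per arm and all patients contributing 6-month data:

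| 6-month rates | 38 per arm | 45 per arm |
|---|---|---|
| 50% vs 80% | 80% | 87% |
| 50% vs 70% | 43% | 49% |
| 50% vs 65% | 26% | 29% |

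**Step 4: a stricter stop.** With 0.001 at 6 months and 0.049 at 12 months, the overall error is 4.9% to 5.0% for every r from 0 to 0.95. The Step 1 formula at 0.049 gives 38.7, still 39 evaluable. Under 50% versus 80% at 6 months, the chance of stopping falls to about 28% (38 per arm) to 38% (45 per arm).

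**The case against.** The strongest reply is that the article never says 0.05 applies at 6 months. It is a condensed report, and a boundary may be set in a full protocol or analysis plan that is not shown. That stands as a limit on the claim: the level is inferred, because it is the only one the article gives. It does not remove the point. The article itself states a binding stop, a single threshold, and a sample size that uses the whole 5% once, and these conflict as written.

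A reader might go further in three ways that the article does not support.

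- **Two-sided testing at both looks.** This would give 9.1%, 8.3% and 7.0% at correlations 0.5, 0.7 and 0.9. It counts a 6-month result favouring control as a reason to stop, whereas the rule in 2.2 stops only for benefit. A 12-month adherence measure that includes the first 6 months would also make the correlation high, which favours the lower end of the range in Step 2.
- **That the trial, on its own assumptions, would usually never reach 12 months.** Section 2.8 attaches no time point to 50% versus 80%, and 2.2 places the primary assessment at 1 year. Nothing says the full effect is present at 6 months, so the 80% to 87% is conditional.
- **That the article's own case for 1-year follow-up rests on continuing discontinuation.** The Introduction does say that "more than one-third of patients discontinue treatment after 6 months, and around half do so within a year", but as general background and not as the reason for the follow-up length. Section 2.3 enrols patients already on all three drugs for at least 6 months and already poorly adherent, so trial months 6 to 12 need not match those time points.

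**Conclusion.** The concern holds. With significance taken at 0.05, the stopping rule does not keep the stated 5%. The excess is modest: an overall error of about 6% to 7% over the plausible range of an unstated correlation, and above 5% for any correlation short of 1. The loss of the 1-year assessment and of the last two group sessions if the rule fires follows from the text alone. How likely that is depends on the 6-month effect, which the article does not state. The wording needs correcting before the trial relies on it, because it affects both the error rate and the time point of the primary result.

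**What to change.** Preferred: in 2.2, make the 6-month evaluation descriptive, remove the stop, and follow all patients to the 12-month primary assessment. This restores the 5% with no extra patients.

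If an efficacy stop is kept, state in 2.2 and 2.7 that it applies to the primary adherence variable, requires p<0.001 at 6 months, and is followed by a 12-month test at 0.049. The sample size is essentially unchanged. By contrast, equal levels at both looks would cost patients: at 0.0294 each (r about 0.71), 45 evaluable and 53 enrolled per group.

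Either change takes one or two sentences. The price is a lower chance of stopping early: none with a descriptive look, and about 28% to 38% with the strict boundary even if the full planned difference is present at 6 months. A strict stop, if it fired, would still forgo the 1-year assessment, which is why the descriptive look is preferred.
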